##### Anthropometry

Anthropometric measurements are taken during a physical education (PE) lesson. Standing height, weight, and waist circumference are measured by researchers or research assistants according to a standardized protocol. Shoes have to be taken off. The children are weighed with a digital weighing scale to the nearest 0.1 kg (Seca weighing scale 803). Height is measured with a stadiometer to the nearest 0.1 cm (Seca 213). Weight and height are used to calculate the Body Mass Index (BMI), which is adjusted for age and gender (BMI z-scores) using the values of a Dutch reference population [48]. Waist circumference is measured with a measuring tape to an accuracy of 0.1 cm (Seca 201). The measuring tape is placed around the umbilicus [49].

##### Physical fitness test

The 15 m endurance shuttle run test, known as the Progressive Aerobic Cardiovascular Endurance Run (PACER), is used to assess the children’s aerobic fitness [50]. The PACER is an item of the EUROFIT test battery [51]. The test is administered during the same PE lesson in which the children’s anthropometric measurements are taken. The assessment of the test lasts between 10 and 15 min. The physical fitness test is not conducted during the time that the children wear the accelerometer.

#### Parents

Parents are requested to fill in a questionnaire during the one-week measurement period at baseline and at follow-up (March and April 2017, 2018 & 2019).

##### Questionnaire

The parent questionnaires are handed to the children, and the parents complete them at home. The questionnaires assess demographics, parent’s PA pattern routines, PA parenting practices, family health climate, child’s NB, anthropometry, and parental school involvement. At follow-up, parents of the intervention schools also receive evaluation questions concerning the KEIGAAF intervention (Table 2).

**Table 2 Tab2:** Concepts, number of items, and example question of the school-based parent questionnaire

Concept	N items	Items
Demographics	22	Name of school child, child’s grade (4th, 5th, 6th), gender of child, birth date of child, birth date of parent, birth date of partner, postal code, relation to child (mother, stepmother, father, stepfather, guardian, other), country of birth, highest education level (no education, primary school, pre-vocational school, secondary education, lower vocational education, higher vocational education, university), hours per week of paid employment (no paid job, 16 or less, 17–24, 25–32, more than 32 h), member of sports club (yes/no), family situation (living together with a partner, single, other) / *Partner*: relation to child, country of birth, highest education level, hours per week of paid employment, member of sports club / number of children (1, 2, 3, 4 or more), number of cars (1, 2, 3 or more).
Parents’ PA transportation routines (PATRns) [80]	4	Example: If I have to go somewhere nearby, I am always inclined to take the bike or to go on foot. (5-point Likert scale: 1 = completely disagree, 5 = completely agree)
PA parenting practices [81]	6	Parental logistic support and restrictions on access to sedentary activities. Example: I enroll my child in sports teams and clubs such as soccer, basketball, and dance. (4-point Likert scale: 1 = completely disagree, 4 = completely agree)
Family health climate [82]	31	Family climate regarding PA and nutrition. Example: In our family… a healthy diet plays an important role in our lives. (4-point Likert scale: 1 = completely disagree, 4 = completely agree)
Child’s nutrition behavior [77]	25	Breakfast consumption, fruit intake, vegetable intake, candy intake, cookie intake, snack intake (0 to 7 days; amount of portions per day), sugar-sweetened beverages consumption, light soda consumption, fruit juice consumption, sweet milk drinks consumption, milk consumption, water and tea without sugar consumption (0 to 7 days; amount of glasses per day)
Anthropometry	3	Weight and height of child, weight and height of parent, weight and height of partner.
Parental school involvement	5	Contact with teacher (5-point Likert scale: 1 = never; 5 = every week), assisting school with school activities (5-point Likert scale: 1 = never; 5 = always), attending parental meeting (5-point Likert scale: 1 = never; 5 = always), feeling welcome at school (5-point Likert scale: 1 = not welcome; 5 = welcome), reading school information (5-point Likert scale: 1 = never; 5 = always).
KEIGAAF evaluation (added at follow-up) *only for intervention group*	6	Aware of KEIGAAF (not aware, heard of it, fully aware), general impression of KEIGAAF (5-point Likert scale: 1 = very bad; 5 = very good), involvement in KEIGAAF (5-point Likert scale: 1 = very little; 5 = very much), experiencing changes at school as a result of KEIGAAF (5-point Likert scale: 1 = very little; 5 = a lot), experiencing changes at home as a result of KEIGAAF (5-point Likert scale: 1 = very little; 5 = a lot), importance of KEIGAAF (5-point Likert scale: 1 = very unimportant; 5 = very important)

##### Questionnaire on family-based intervention

The questionnaire related to the family-based intervention is filled in at the start and at the end of the intervention (after three months) by participants of the Lifestyle Triple P intervention. The questionnaire assesses general parenting practices [52], nutrition parenting practices [53, 54], and PA parenting practices [13, 55, 56]. Questions to evaluate and improve the program are included in the follow-up questionnaire.

### Process evaluation

An elaborate process evaluation will be conducted in which the processes involved in the implementation of KEIGAAF and contextual factors influencing these processes are illuminated. For this, a mixed-methods approach will be used: 1) an activity checklist is filled in throughout the implementation period to gain insight into what is implemented by the different KEIGAAF working groups; 2) a quantitative team climate checklist is filled in at baseline, after one and after two years. This checklist provides information about the climate for innovativeness within a working group [57, 58]; 3) school policy documents are collected, providing information about policies influencing intervention implementation; 4) participant observations of the working groups and semi-structured interviews with working group members are conducted to gain additional knowledge about factors inhibiting or facilitating implementation; and finally, 5) the data of the environmental scan and the school scan provide insight into neighborhood and school factors impeding or facilitating intervention success. Data is collected throughout the implementation period of the combined school- and family-based interventions. The timeline of the KEIGAAF project is shown in Fig. 3.

### Data analysis

Descriptive statistics will be used for baseline data. Accelerometer data will be analyzed using Actilife (Version 6.13.3). To correct for nesting of the data, multilevel regression analyses will be used to analyze it. When studying intervention effects, baseline data will be taken into account as possible confounders. Using forward selection, the random and fixed effects part will be further refined by likelihood ratio tests. Intervention effectiveness will be tested at T1 (after one year) and at T2 (after two years). A two-sided test with a type I error rate of 5% will be used. Statistical analyses will be conducted using SPSS 24.0 (IBM Corp, USA).

Quantitative process data will be analyzed with SPSS. Inductive content analysis will be performed to analyze the qualitative process data. Interviews will be transcribed verbatim, and themes and concepts arising from the data will be coded. Outcomes of the process evaluation will be linked to the outcomes of the effectiveness study to clarify the effects on the primary and secondary outcome measures.

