**Methods:**

A quasi-experimental, controlled study with eight intervention schools and three control schools was conducted. The KEIGAAF intervention consists of a combined top-down and bottom-up school intervention: a steering committee developed the general KEIGAAF principles (top-down), and in accordance with these principles, KEIGAAF working groups subsequently develop and implement the intervention in their local context (bottom-up). Parents are also invited to participate in a family-based parenting program, i.e., Triple P Lifestyle. Children aged 7 to 10 years old (grades 4 to 6 in the Netherlands) are included in the study. Effect evaluation data is collected at baseline, after one year, and after two years by using a child questionnaire, accelerometers, anthropometry, a physical fitness test, and a parent questionnaire. A mixed methods approach is applied for the process evaluation: quantitative (checklists, questionnaires) and qualitative methods (observations, interviews) are used. To analyze intervention effectiveness, multilevel regression analyses will be conducted. Content analyses will be conducted on the qualitative process data.

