## Methods

### Study design

The aim of the KEIGAAF project is to design and test the effectiveness of the school- and family-based intervention on the primary outcome measure (BMI z-score) and the secondary outcome measures (PA behavior, sedentary behavior and nutrition behavior, physical fitness, and waist circumference) of children aged 7–10 years living in low socio-economic neighborhoods.

A convenience sample of intervention schools was recruited in Eindhoven, a relatively large city in the southern part of the Netherlands. Schools were eligible if: 1) they were located in a low socio-economic neighborhood; 2) they had no plans to merge with another school or to relocate in the coming three years, and if; 3) the school staff was willing to participate actively in KEIGAAF and to collaborate with parents and local partners, for instance, sports professionals, social workers, and/or municipality officers. The steering committee of the KEIGAAF project, consisting of researchers from Maastricht University and Fontys University of Applied Sciences (School of Sports Studies) and local partners from a school board, a sports support organization, and a social welfare organization, identified nine eligible schools. All nine schools were contacted and informed about the project, and eight schools agreed to participate. Because of the active participation of the intervention schools in the development and implementation of the intervention, no randomization was applied.

Control schools were recruited in Maastricht, a city comparable to Eindhoven based on the level of urbanization and the socio-economic status of the neighborhoods. Three schools agreed to participate in the study; these schools did not apply the KEIGAAF intervention (Fig. 1). Due to the distance between Eindhoven and Maastricht (approximately 90 km), a low risk of contamination is expected. KEIGAAF is funded by Fonds NutsOhra, project number 101.253, and the trial is registered as NTR6716. Ethical approval was obtained from the medical ethics committee of the Maastricht University Medical Centre (METC163027, national number: NL58554.068.16).

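### Forward selection by likelihood ratio test in a non-randomised two-city comparison can drop weak but imbalanced confounders; a core adjustment set should be kept regardless of significance

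*Protocol article*

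**What the plan says.** The Data analysis section of the protocol article sets out the effect model in a few sentences. Multilevel regression handles the nesting. On confounding it says that, for intervention effects, "baseline data will be taken into account as possible confounders". On model building it says "Using forward selection, the random and fixed effects part will be further refined by likelihood ratio tests". On the test it says "A two-sided test with a type I error rate of 5% will be used", applied at one year and at two years. No covariate is named as always retained, and no entry level for the likelihood ratio tests is given.

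The Study design section describes the comparison to which this applies. "A convenience sample of intervention schools was recruited in Eindhoven", and staff willingness to take part actively was an eligibility criterion. The three control schools come from another city, described as comparable on urbanisation and neighbourhood socio-economic status. The section states that "no randomization was applied".

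The selection sentence also covers the random part. Only the fixed part, and so the confounders, is examined here.

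**The concern.** In a randomised trial, the choice of covariates mainly affects precision. Here it also affects bias. The bias from omitting a covariate is its association with the outcome multiplied by its difference between the groups. A likelihood ratio test for entry, with the intervention term already in the model, responds only to the first factor. Two covariates with the same outcome effect have the same chance of entry even if one is balanced and the other differs by half a standard deviation between the cities. The rule can thus discard a covariate that matters for the comparison because it adds little to the fit.

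At stake is the intervention effect on BMI z-score and on the secondary outcomes. It would carry confounding that variables already collected in the study could remove.

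**Working it through.** **Inputs from the article.** 419 intervention and 104 control children (N = 523); 8 and 3 schools; school/class ICC from 0.005/0.025 to 0.025/0.005; two-sided 5%. The stated detectable differences are 0.38 to 0.44 at 80% power and 0.44 to 0.51 at 90%.

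**Assumed, because not stated.** SD of BMI z-score 1.0; 3 classes per school; entry at p < 0.05; intervention term in the model during selection; independent child-level covariates with SD 1, all biasing in the same direction.

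**Step 1: the article's own precision.** Variance of the effect = sum over the two groups of ICC_school/k + ICC_class/(3k) + (1 − ICC_school − ICC_class)/n.
- ICC 0.005/0.025: 0.005 × 0.4583 + 0.025 × 0.1528 + 0.97 × 0.0120 = 0.0178, so SE = 0.133. Detectable difference 2.80 × 0.133 = 0.373 (80%) and 3.24 × 0.133 = 0.432 (90%).
- ICC 0.025/0.005: 0.025 × 0.4583 + 0.005 × 0.1528 + 0.97 × 0.0120 = 0.0239, so SE = 0.154. Detectable difference 0.433 (80%) and 0.501 (90%).

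All four are within 2% of the stated figures, so these standard errors are a fair basis.

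**Step 2: how often a true confounder is dropped.** The entry statistic is roughly normal with mean b × √523, where b is the outcome effect per SD. The group difference d does not appear in it.
- b = 0.05: mean 1.14, dropped in about 79% of samples.
- b = 0.08: mean 1.83, about 55%.
- b = 0.12: mean 2.74, about 22%.
- b = 0.30: mean 6.86, practically never.

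**Step 3: effect on the test.** Simulation with a true null intervention effect. The clustered runs use school/class ICC 0.025/0.005, known variance components and 3,000 replicates (Monte Carlo error about 0.4 to 0.5 percentage points).

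| Confounders | d (SD) | b | Type I error, forward selection | Type I error, all forced in | Mean bias, forward selection (SD) |
|---|---|---|---|---|---|
| 5 | 0.3 | 0.08 | 6.9% | 5.4% | 0.039 |
| 5 | 0.5 | 0.05 | 8.6% | 4.9% | 0.073 |
| 5 | 0.5 | 0.08 | 8.8% | 4.7% | 0.063 |
| 1 | 0.5 | 0.08 | 5.5% | 4.7% | 0.009 |
| 5 | 0 | 0.08 | 5.5% | 5.5% | 0.000 |
| 5 | 0.5 | 0.30 | 5.5% | 5.5% | 0.003 |

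Ignoring clustering (10,000 replicates), five confounders with d = 0.3 to 0.5 and b = 0.05 to 0.12 give 7.8 to 13.4% with selection against 5.0 to 5.5% forced in. The clustered figures are lower because a similar bias is set against a larger standard error. They are the relevant ones for this study.

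**Step 4: scale.** In the first three rows the bias is 0.039 to 0.073, that is 0.039/0.44 = 9% to 0.073/0.44 = 17% of the detectable difference stated for this ICC at 80% power.

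**The case against.** **The wording leaves room.** The phrase about further refinement could mean that some baseline terms are already in the model before selection starts. A looser entry level would also drop fewer confounders. Both points are fair. But the text names no term that stays in, so the selection rule is what a reader has to go on. If a fixed core is intended, stating it is the same change.

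**The article is condensed.** A full covariate list and the handling of missing items may well stand in a document not shown, and their absence is not the criticism. The criticism is of the selection method, which the article does fix. It does not say whether selection is repeated for each outcome and time point. A reader might infer a different adjustment set for each, but that would rest on silence.

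**Other protection exists.** A reader might infer that adjustment is the only safeguard. It is not: "Control schools were recruited in Maastricht, a city comparable to Eindhoven based on the level of urbanization" and on neighbourhood socio-economic status, and the same grades are enrolled in both groups. These features limit confounding at city and grade level. They do not balance child and family characteristics among those who consented (61.3% and 56.8%).

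**The most important covariate is probably safe.** Baseline BMI z-score should predict follow-up BMI z-score strongly, and strong covariates are practically never dropped. This stands, and it confines the problem to weaker confounders.

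**Conclusion.** The point holds as a weakness of method. Selecting on outcome fit alone does not suit confounder control in this design, and it can leave avoidable bias. It does not invalidate the analysis.

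The size is not known from the article. The figure of about 7 to 9% type I error, against about 5%, rests on five weak confounders imbalanced by 0.3 to 0.5 SD in the same direction and on entry at 5%. Confounders that bias in opposite directions would partly cancel.

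Two stronger readings are not supported:
- A reader might infer 6 to 10% type I error for each omitted covariate. This takes a coefficient exactly at the entry boundary (1.96/√523 = 0.086) and multiplies it by an imbalance of 0.5 to 1.0 SD, giving 0.04 to 0.09, or 0.28 to 0.64 standard errors. That is a worst case, and nothing in the article points to such an imbalance. A single confounder at 0.5 SD gives 5.5% with clustering and 5.6 to 5.7% without.
- A reader might infer that the p-value is wrong simply because selection is ignored. With five screened covariates and no imbalance, type I error is 5.5% under both approaches with clustering, and 5.5% against 5.3% without. The harm is residual confounding, not selection as such.

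**What to change.** State in Data analysis that a core set stays in every effect model regardless of significance: baseline value of the outcome, age or grade, sex, parental education and country of birth. Report any forward-selected model only as a sensitivity analysis. For BMI z-score, age and sex are already in the score and add little, so the working additions there are the baseline value, parental education and country of birth.

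All of these are already collected. Tables 1 and 2 list the child and parent items, and the outcomes are measured at baseline. The article reports data collection as ongoing, so at that stage the set could still be fixed before the two-year analysis.

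The costs are small:
- A few degrees of freedom among 523 children.
- A slightly wider standard error. A covariate imbalanced by 1 SD adds about 1/523 = 0.0019 to a variance of 0.0178 to 0.0239, and √(0.0197/0.0178) = 1.05 and √(0.0258/0.0239) = 1.04, so about 4 to 5%. At 0.5 SD the addition is a quarter of that, and the widening about 1%.
- A stated method for missing parent-reported items. This chiefly concerns parental education, since the child questionnaire also asks for the child's and parents' country of birth.

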### Power calculation

Children’s health outcome, i.e., BMI z-score, is the primary outcome measure in this study, while interventions are targeted on more distal health behaviors (EBRBs). EBRBs are used as additional outcome measures and considered as predictors of BMI z-scores. Therefore, baseline measurements of the participants’ BMI z-score were used to calculate the power of the study. At baseline, 419 intervention children and 104 control children were included in the study. Children were in grade 4, 5, or 6. In two-level, school-based, cluster randomized trials with BMI z-score as the outcome, the intra-class correlation (ICC) was mostly 0.03 or smaller (e.g., [59–61]). Taking a three-level design into consideration, it is assumed that the ICC ranges from 0.005 for the school level and 0.025 for the class level to an ICC of 0.025 for the school level and an ICC of 0.005 for the class level. For the given sample size, the smallest detectable difference in BMI z-score after two years of intervention ranges between 0.38 and 0.44 when the power is 80%, and between 0.44 and 0.51 when the power is 90%. Using Lipsey’s [62] cut-off scores, this indicates a moderate effect. Empirical results show that differences of this size are attainable for combined school- and family-based interventions [63, 64]. Although the effects are moderate, they may lead to clinical significant effects at the population level if they are sustained for several years [65].

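### Forward likelihood-ratio selection of the random part does not exempt the school and class intercepts; if it reaches them, the nominal 5% test runs at about 7–13%

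*Protocol article*

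**What the plan says.** The protocol article, Methods, Data analysis, first gives the reason for the model: "To correct for nesting of the data, multilevel regression analyses will be used to analyze it". It then gives the rule for building it: "Using forward selection, the random and fixed effects part will be further refined by likelihood ratio tests". The effect test follows: "A two-sided test with a type I error rate of 5% will be used". Effectiveness is tested after one year and after two years. Nothing in the section says that the school or class intercept is kept when its likelihood-ratio test is not significant.

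Two other places bear on this. The abstract gives the design: "A quasi-experimental, controlled study with eight intervention schools and three control schools was conducted". Under Power calculation the article adopts a three-level design, in which "it is assumed that the ICC ranges from 0.005 for the school level and 0.025 for the class level" to the reverse pair, 0.025 for school and 0.005 for class.

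**The concern.** The intervention varies only between schools. Clustering by school is therefore a feature of the design, and a non-significant variance test on 11 schools does not show that it is absent. With school ICCs of 0.005 to 0.025 such a test has little power, so a forward rule that covers the intercepts will often leave out the very level that the multilevel model was chosen to handle.

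Once the school intercept is out, the standard error of the intervention effect is too small. The effect is then judged as if hundreds of children, and not 11 schools, carried the information. An ineffective intervention would be declared effective more often than the stated 5%, on the primary outcome and at both time points. The fitted model would also lack the clustering terms that the power calculation assumes.

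**Working it through.** **Inputs from the article.** Eight and three schools; "At baseline, 419 intervention children and 104 control children were included in the study"; two-sided 5%; the two ICC pairs above.

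**Assumptions, not in the article.** Three classes per school, one per grade (the article says only "Children were in grade 4, 5, or 6"); SD of the BMI z-score 1; equal sizes within an arm; no dropout; ICCs unchanged by baseline adjustment.

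**Step 1: reproduce the plan's detectable differences.** For an arm with n children, let nS be children per school and m = nS/3 children per class. Write ρs and ρc for the school and class ICCs.

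- Design effect: D = 1 + (m − 1)(ρs + ρc) + (nS − m)ρs
- Variance of the arm difference: V = D₁/419 + D₀/104
- Detectable difference: (1.960 + z) × SD × √V, with z = 0.842 for 80% power and 1.282 for 90%

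Here nS = 419/8 = 52.4 and 104/3 = 34.7, so m = 17.5 and 11.6.

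| ICC school / class | D₁ | D₀ | V | 80% power | 90% power |
|---|---|---|---|---|---|
| 0.005 / 0.025 | 1.668 | 1.432 | 0.01775 | 0.373 | 0.432 |
| 0.025 / 0.005 | 2.367 | 1.894 | 0.02386 | 0.433 | 0.501 |

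The article states 0.38 to 0.44 and 0.44 to 0.51. All four figures agree within 2%, and an SD of 1.02 matches them. Without clustering, V = 1/419 + 1/104 = 0.01200 and the differences would be 0.307 and 0.355. So the stated power carries both levels of clustering.

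**Step 2: the limiting case with no random effect kept.** The true error rate is 2[1 − Φ(1.96/√(V/0.01200))].

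- ICC 0.005 / 0.025: ratio 1.479, error rate 10.7%
- ICC 0.025 / 0.005: ratio 1.988, error rate 16.5%

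**Step 3: forward selection, by simulation under no effect.** There were 8,000 replicates per scenario, with 8 × 3 × 17 children against 3 × 3 × 12. Arm was fixed, and an intercept entered only if its likelihood-ratio test passed chi-square(1) at 5%. Ranges cover different orders of testing school and class. The arm effect is tested against the normal distribution. The Monte Carlo standard error near 10% is √(0.1 × 0.9/8000), about 0.3 percentage points. The middle ICC pair is an added intermediate case.

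| ICC school / class | Fit | School left out | Error after selection | Error, both kept |
|---|---|---|---|---|
| 0.005 / 0.025 | REML | 81–93% | 7.9–8.1% | 5.4% |
| 0.005 / 0.025 | ML | 89–96% | 8.7–8.8% | 6.4% |
| 0.015 / 0.015 | REML | 68–83% | 9.9–10.3% | 6.6% |
| 0.015 / 0.015 | ML | 77–89% | 11.1–11.5% | 8.1% |
| 0.025 / 0.005 | REML | 54–68% | 10.8–11.4% | 7.3% |
| 0.025 / 0.005 | ML | 65–77% | 12.5–13.0% | 8.9% |

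The difference between the last two columns is the part due to selection with estimator and reference held fixed: from 8.7 − 6.4 = 2.3 points to 11.4 − 7.3 = 4.1 points.

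**Step 4: variations.**

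- Half-mixture chi-square cut-off, which suits a variance on its boundary. At school ICC 0.025 with REML and school tested first, omission falls to 45% and the error rate is 9.7%. At 0.005 the error rate is 7.2–8.2%.
- Smaller classes (14 and 9 children, ML): 8.7–12.0%.
- Five classes per intervention school (REML): 8.2–10.5%.
- A t reference on 9 degrees of freedom, used only when school is kept, helps little: at school ICC 0.025 under REML the rate is 9.9–10.7%. With both intercepts always kept, t(9) gives 2.8–3.9% (REML) or 3.6–5.3% (ML) over the ICC range.

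**The case against.** The strongest reply concerns the reading. The section first adopts a multilevel model to deal with nesting and only then refines it. The word *further* presupposes a starting model, and forward selection adds to a base. On that reading the intercepts are already in, and the tests decide only on extra terms such as random slopes. The three-level power calculation fits that intention. This reading is reasonable, and under it the inflation from selection does not arise. An intermediate reading, with school always kept and only class tested, is also nearly harmless: a separate simulation gave 2.9–4.8% with t(9), against 2.5–4.6% with both intercepts kept.

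A second reply is that the base model, the estimator and the degrees of freedom are detail that an article leaves to an analysis plan. That holds for the estimator and the degrees of freedom, so their absence is not the point here. The selection rule, however, is stated, it names the random part, and it carries no exception.

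A third reply is that a contrast between selection under ML and always-kept intercepts under REML with t(9) changes several things at once. That is correct. It is why the table compares like with like and why some of the excess is put down to the small number of schools.

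**Conclusion.** The point stands in conditional form. The stated rule covers the random part without protecting the school and class intercepts. If it is applied to them, the nominal 5% test of the intervention effect runs at about 7–13% under the protocol's own ICCs, and selection itself accounts for roughly 2 to 4 percentage points of that against a normal reference. The rest comes mainly from having few schools, most visibly under ML. The figures rest on the assumptions listed with the inputs. The ICC after baseline adjustment is unknown and could be higher or lower.

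A reader might infer two stronger things. One is that the plan will discard the school effect; the text does not say so, because the sentence can be read as adding to a model that already contains it. The other is that the school intercept would usually be dropped whatever the ICC. That fits school ICC 0.005, but at 0.025 omission is a modest majority (54–77%), and 45% in one variant.

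**What to change.** Add one sentence to the analysis section: random intercepts for school and class are included in every effect model whatever their significance or estimated size, and likelihood-ratio selection is limited to other terms. If the intercepts were always meant to stay, this only makes the intention explicit.

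Preferably also state that models are fitted by REML with small-sample degrees of freedom (for example Satterthwaite) for the intervention effect. Retention alone, with a normal reference, still leaves 5.4–7.3% under REML and 6.4–8.9% under ML. An analysis of the 11 adjusted school means is an optional sensitivity analysis.

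The cost is wider, slightly conservative intervals. As a guide, replacing the normal quantiles in Step 1 by t on 9 degrees of freedom moves the detectable difference (SD 1) from 0.373–0.433 to 0.419–0.486 at 80% power. The article says that data collection is still under way, so the sentence can be settled before the effect analyses.

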### Family-based intervention

A family-based parenting program was implemented stepwise from September 2017. The family-based program (Lifestyle Triple P) mainly targets parents whose children are overweight or obese. The aim of the intervention is to improve energy balance-related parenting practices [33, 44]. In eight group sessions and four one-on-one home sessions, Lifestyle Triple P coaches coach parents in positive parenting, nutrition-related parenting practices, and PA-related parenting practices, to support parents in creating a healthy home environment. While the parents attend the Triple P Lifestyle group sessions, their children participate in active fun group play provided by sports students or physical education teachers.

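### BMI z-score is tested at one year and at two years under one 5% level with no deciding time point, while the power calculation covers a single comparison labelled two years

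*Protocol article*

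**What the plan says.** The Study design section sets out to test the "effectiveness of the school- and family-based intervention on the primary outcome measure (BMI z-score") and attaches no time point to that outcome. The Data analysis section then states the testing rule: "Intervention effectiveness will be tested at T1 (after one year) and at T2 (after two years"). The next sentence gives the level: "A two-sided test with a type I error rate of 5% will be used". No split of the 5%, no order of testing and no deciding time point is given. The opening of the Discussion again presents one-year and two-year effects side by side, unranked.

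Only the Power calculation section singles out a time point. It reports "the smallest detectable difference in BMI z-score after two years of intervention" as 0.38 to 0.44 at 80% power and 0.44 to 0.51 at 90% power. It does not call two years the primary time point.

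**The concern.** The Data analysis section announces two tests of the primary outcome; the Power calculation section sizes the study for one. A single 5% level with no split is most naturally read as applying to each test. On that reading the study has two chances to find the intervention effective on BMI z-score, and the error rate for the primary question is above the stated 5%. On the other reading, with the 5% shared, power at the quoted differences is lower than quoted.

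The practical stake is a discordant result. If one year is significant and two years is not, or the reverse, the article as written does not settle whether the primary question has been answered positively.

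**Working it through.** **Inputs from the article.** 8 intervention and 3 control schools (Study design); "At baseline, 419 intervention children and 104 control children were included in the study"; intra-class correlations (ICCs) running from school 0.005 with class 0.025 to school 0.025 with class 0.005 (Power calculation); two-sided 5% (Data analysis).

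**Assumed, because not given.** Three classes per school (one per grade), so 24 and 9 classes; the SD of BMI z-score; the correlation between the one-year and two-year test statistics.

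**Step 1: reproduce the stated detectable differences.** Normal approximation for three levels:

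MDD = (z for alpha + z for power) × SD × √V, where V is the sum over the two arms of [ICC_school/schools + ICC_class/classes + (1 − ICC_school − ICC_class)/children].

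- School 0.005, class 0.025: V = (0.005/8 + 0.025/24 + 0.97/419) + (0.005/3 + 0.025/9 + 0.97/104) = 0.00398 + 0.01377 = 0.01775; √V = 0.1332.
- School 0.025, class 0.005: V = (0.025/8 + 0.005/24 + 0.97/419) + (0.025/3 + 0.005/9 + 0.97/104) = 0.00565 + 0.01822 = 0.02386; √V = 0.1545.
- Multipliers at two-sided 5%: 1.960 + 0.842 = 2.802 (80% power) and 1.960 + 1.282 = 3.242 (90%).

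| SD | 80% power | 90% power |
|---|---|---|
| 1.00 | 0.373 to 0.433 | 0.432 to 0.501 |
| 1.015 | 0.379 to 0.439 | 0.438 to 0.508 |
| Article | 0.38 to 0.44 | 0.44 to 0.51 |

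With SD 1.015 all four figures round to those stated. The calculation is thus consistent with the full 5% being spent on one comparison. Because the SD is free, this is not proof. At 2.5% per test (multipliers 2.241 + 0.842 = 3.083 and 2.241 + 1.282 = 3.523), an SD of 0.93 gives 0.382 to 0.443 and 0.437 to 0.506, which also round to the stated values. The full-5% reading rests on the text: 5% is the only level the article gives, and no split is mentioned.

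**Step 2: false-positive rate if either test can support the claim.** With each test at two-sided 5% and correlation r between the statistics, the rate is 1 − P(|Z1| < 1.96 and |Z2| < 1.96), bivariate normal:

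| Assumed r | Chance of at least one false positive |
|---|---|
| 0 (independent: 1 − 0.95²) | 9.75% |
| 0.5 | 9.1% |
| 0.8 | 7.8% |
| 0.9 | 7.0% |
| 0.95 | 6.5% |

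The rate returns to 5% only at perfect correlation. Both tests measure the same outcome in the same children a year apart, so the strongly correlated rows are the more plausible.

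**Step 3: power if the 5% is split equally.** Take the stated differences as those detectable at the full 5%.

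- 80% power becomes Φ(2.802 − 2.241) = Φ(0.560) = 71%.
- 90% power becomes Φ(3.242 − 2.241) = Φ(1.000) = 84%.
- To regain 80%, the detectable difference grows by 3.083/2.802 = 1.100, to about 0.42 to 0.48. To regain 90%, it grows by 3.523/3.242 = 1.087, to about 0.48 to 0.55.

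**The case against.** The strongest reply is that a condensed article may leave the deciding time point and the handling of multiplicity to a full protocol or analysis plan, and that testing at one and two years is not wrong in itself. The Data analysis section fixes when tests are done; it does not say that success at either is enough. The reply adds that the article leans towards two years: that is the only time point in the power calculation, and the Planning section has implementation running until the final measurements.

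Part of this stands. The either-test rule is a reading, which is why the result above is conditional, and the word each does not appear beside the 5%. The pointer to two years is real, but it is an inference. What remains is not silence: the article states two tests under one 5% level and a power calculation for one comparison, and these need one more statement to agree.

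Three stronger readings may tempt a reader and are not supported:

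- **That one year is underpowered.** The calculation uses baseline numbers, and the formula that reproduces it has no time term. With the same number of children it would give the same detectable difference at one year. Two years is a label on the calculation.
- **That one year cannot reflect the combined intervention.** The Family-based intervention section says "A family-based parenting program was implemented stepwise from September 2017", and its closing questionnaire comes after three months. Families who started that autumn could have finished before the March and April 2018 measurements. Stepwise rollout may mean that others had not, but the article does not show that one year is uninformative, and the point has no bearing on the error rate.
- **That the error rate is nearly doubled.** The 9.75% figure needs independent tests, which is implausible for repeated BMI z-scores.

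**Conclusion.** The point holds as an inconsistency between two stated parts of the article: two tests of the primary outcome under a single 5% level, and a power calculation for one comparison. If either test may support the claim, the false-positive rate is about 6.5% to 9.1%. This rests on assumed correlations of 0.95 to 0.5 and on each test having its nominal size. If the 5% is shared equally, power at the stated differences is about 71% and 84% instead of 80% and 90%. This rests on the stated differences having been computed at the full 5%, the only level given.

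The excess is modest and the ambiguity is easily removed. It should be corrected because the choice of deciding time point governs what a discordant pair of results would mean. It does not show that either comparison is invalid.

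**What to change.** Add to the Data analysis section: the primary comparison is BMI z-score at T2 (two years), tested two-sided at 5%; the comparison at T1 (one year) is secondary and is interpreted confirmatorily only if T2 is significant.

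This agrees with the label in the Power calculation section, holds the error rate of the primary claim at 5%, and leaves the stated detectable differences unchanged. The fixed order lets T1 also be tested at 5% without raising the overall rate for the pair. No further data or change of model is needed. The Data collection section describes collection as unfinished, so the rule can be set before two-year results are known.

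The cost is that an effect present only at one year could be reported but not claimed as the primary result. If the investigators want either time point to count, they should state how the 5% is divided and restate the power accordingly, as in Step 3 of the working.
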